**5.3 INTERVENTION**

During the randomisation, patients with be randomly allocated to the experimental or control group (Figure 2):

- 1. Experimental group: standard of care at the discretion of the researcher, including lopinavir/ritonavir (200/50 mg orally, 2 tablets q12h for 7 to 14 days) ± remdesivir (200 mg loading dose intravenously on day 1, followed by 100 mg/day for 5 to 10 days), or no drug treatment, plus pulsed methylprednisolone (120 mg/day intravenously on days 1, 2 and 3).
  2. Control group (standard): standard of care at the discretion of the researcher, including lopinavir/ritonavir (200/50 mg orally, 2 tablets q12h for 7 to 14 days) ± remdesivir (200 mg IV on the first day, followed by 100 mg/day for 5 to 10 days), or no drug treatment, plus placebo* (intravenously on days 1, 2 and 3).

*Note: placebo consists of 100 ml of 0.9% sodium chloride.

The doses of methylprednisolone (120 mg IV) or placebo (NaCl 0.9% IV) will be prepared and dispensed by the hospital pharmacy. Only the staff responsible for preparing the medication will know patient group allocation. That is, neither the researcher nor nurses administering the treatment will know the content of the bags supplied.

Patients in both groups will be treated with tocilizumab if at any point the following are observed:

- Decrease in PaO_2_ ≥15% from baseline + laboratory or radiological deterioration and/or
- SpO_2_ in ambient air falling to < 90% or PaO_2_ in ambient air < 60 mmHg or PaO_2_/FiO_2_ below 300 mmHg not explained by any other condition.

**5.4 FOLLOW-UP METHODS**

**5.4.1 Baseline assessment**

All the patients included in the study will be assessed at baseline in the emergency department or on the hospital ward. This baseline assessment will include the following elements:

- Guided clinical history
- Medical history and comorbidities
- Concomitant treatments
- Vital signs: temperature, blood pressure, heart rate, respiratory rate and oxygen saturation
- Physical examination
- Blood tests: blood count, coagulation tests including D-dimer, renal function, and levels of CRP, procalcitonin, ferritin, LDH and IL-6
- Chest X-ray (interpreted by a pulmonary radiologist).

**5.4.2 Follow-up**

During hospital admission, patients will be followed-up in accordance with standard procedures for COVID-19 (11), with close monitoring of their vital signs (temperature, blood pressure, heart rate, respiratory rate, and oxygen saturation). All patients in the study will be assessed in person at least once a day by a doctor who is a member of a specialized COVID-19 team, in accordance with the established treatment protocol. The detection of any significant clinical change will prompt an addition assessment of vital signs and medical examination.

Blood tests involving a blood count, coagulation tests including D-dimer, and the measurement of renal function and levels of CPR, procalcitonin, ferritin, LDH and IL-6, will be performed every 48 hours and whenever there is a significant clinical change, at the discretion of the doctor in charge. Further, a chest X-ray will be performed every 48 hours and in the event of a significant clinical change, at the discretion of the doctor in charge, and the results will be interpreted by a pulmonary radiologist.

A follow-up RT-PCR will be performed before administrative discharge and this is to be performed at least 7 days after the first PCR.

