During the previous pandemics caused by coronaviruses (severe acute respiratory syndrome [SARS] and the Middle East respiratory syndrome [MERS]), glucocorticoids were not among the recommended evidence-based treatments, as it seemed that they could be associated with a poorer course of the disease (6). In line with this, the World Health Organisation (WHO) advised against the use of glucocorticoids in the treatment of SARS-CoV-2, given that some studies found these drugs to be associated with a delayed viral clearance, psychosis, complications related to diabetes mellitus, avascular necrosis and even a higher risk of mortality (7).

Despite this recommendation by the WHO, given the poor response to antiviral drugs and growing data on the cytokine release syndrome in COVID-19, the medical community has started to prescribe glucocorticoids empirically in the early inflammatory stage of the disease. Their use in real clinical practice has been supported by more recent publications suggesting that glucocorticoids do benefit patients without significant adverse effects or delayed viral clearance (8, 9), and in Spain, by the inclusion of these drugs in the majority of hospital protocols for COVID-19. Nonetheless, the level of evidence available leaves many questions unanswered, that are difficult to address outside of a comparative clinical trial.

From the molecular point of view, pulsed glucocorticoids over 3 to 5 days at high doses (from 100 mg/day of prednisone or equivalent) work through dual (genomic and non-genomic) mechanisms of action with a low risk of toxicity. That is, as well as strong genomic effects following the complete saturation of the cytosolic glucocorticoid receptors (GRs) and their subsequent translocation into the cell nucleus, high doses lead to non-genomic effects mediated by selective membrane receptors (10). These additional non-genomic effects are associated with strong clinical response that is rapid, as it does not depend on the process of nuclear translocation of the glucocorticoid-GR complex and modulation of gene expression. On the other hand, the majority of adverse events related to glucocorticoids, including infections, are dose- and time-dependent, and hence tend to be associated with long-term maintenance treatments at doses under 100 mg/day of prednisone or equivalent that only activate the genomic pathway.

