**Exclusion criteria:**

- Allergy or contraindication to the drugs under study
- Signs of respiratory failure: SpO_2_ in ambient air < 90% or PaO_2_ in ambient air < 60 mmHg or PaO_2_/FiO_2_ < 300 mmHg
- Need for glucocorticoids or other immunosuppressants (including biologics) for another indication
- Decompensated diabetes mellitus
- Uncontrolled hypertension
- Psychotic or manic disorder
- Active cancer
- Pregnancy or breastfeeding
- Clinical or biochemical (procalcitonin > 0.5 ng/mL) suspicion of active infection with any pathogen other than SARS-CoV-2
- Management as an outpatient
- Conservative or palliative management
- Participation another clinical trial
- Any other major uncontrolled medical, psychological, psychiatric, geographic, or social problem contraindicating patient’s participation in the study or that hinders proper patient follow-up and adherence to the protocol and the evaluation of study outcomes.

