**Independent variables:**

Epidemiological data:

- Date of birth
- Sex.

Comorbidities:

- Exsmoker
- Smoker
- Type 2 diabetes mellitus
- Hypertension
- Hypercholesterolemia
- Kidney failure: stage 1-5
- Obesity: class 1-4
- Ischaemic heart disease
- Cerebrovascular disease
- Peripheral artery disease
- Chronic obstructive pulmonary disease
- Asthma
- Comorbidities as assessed by the Charlson index.

Clinical and hospitalisation-related parameters:

- Date of onset of symptoms
- Date of hospital admission.

Medication taken at home (prior to hospital admission):

- Metformin
- Dipeptidyl peptidase-4 inhibitors
- Sodium-glucose cotransporter-2 inhibitors
- Insulin
- Angiotensin-converting enzyme inhibitors- angiotensin receptor blockers
- Spironolactone
- Inhaled corticosteroids
- Hydroxychloroquine
- Others.

Medication given in hospital:

- Azithromycin, dates of starting and stopping treatment
- Lopinavir/ritonavir, dates of starting and stopping treatment
- Interferon beta-1b, dates of starting and stopping treatment
- Tocilizumab, dates of starting and stopping treatment
- Anakinra, dates of starting and stopping treatment
- Ciclosporin, dates of starting and stopping treatment
- Remdesivir, dates of starting and stopping treatment
- Colchicine, dates of starting and stopping treatment
- Other drugs, dates of starting and stopping treatment.

Baseline blood tests:

- SpO_2_/FiO_2_
- White blood cell count
- Lactate dehydrogenase (LDH)
- D-dimer
- Fibrinogen
- IL-6
- CRP
- Procalcitonin
- Ferritin
- Haemoglobin
- Platelet count.

Follow-up blood tests:

- SpO_2_/FiO_2_
- White blood cell count
- LDH
- D-dimer
- Fibrinogen
- IL-6
- CRP
- Procalcitonin
- Ferritin
- Haemoglobin
- Platelet count.

Radiological findings:

- Lobar pneumonia
- Multilobar pneumonia
- Radiological Severity Score for COVID-19.

Safety-related events (related to glucocorticoids):

- Decompensation of diabetes
- Infection
- Psychosis or mania
- Worsening of hypertension
- Dyspepsia
- Gastrointestinal haemorrhage
- Delay in viral clearance assessed by nasopharyngeal RT-PCR (7 days after the first RT-PCR)
- Others.

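### Diabetic decompensation is a listed glucocorticoid safety event and an exclusion, but the protocol schedules and records no glucose and does not define decompensation

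*Protocol*

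**What the plan says.** Four parts of the protocol bear on glycaemia.

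- **Rationale and aim.** Section 1.1 counts "complications related to diabetes mellitus" among the reported harms of glucocorticoids. The same section and section 1.2 make safety an aim alongside efficacy.
- **Eligibility and withdrawal.** The exclusion criteria in section 4.4 include "Decompensated diabetes mellitus", with no threshold. The withdrawal criteria add that developing an exclusion criterion of clinical relevance to safety can be a reason for withdrawal.
- **Safety variables.** The list of glucocorticoid-related safety events, under Independent variables, opens with "Decompensation of diabetes". No definition is given, and the list closes with a residual category.
- **Measurements.** Section 5.4.1 sets the baseline panel: "Blood tests: blood count, coagulation tests including D-dimer, renal function, and levels of CRP, procalcitonin, ferritin, LDH and IL-6". Section 5.4.2 repeats it every 48 hours and on significant clinical change: "Blood tests involving a blood count, coagulation tests including D-dimer, and the measurement of renal function and levels of CPR, procalcitonin, ferritin, LDH and IL-6" (CPR is evidently CRP). The recorded variables have a baseline list and a matching list headed "Follow-up blood tests". Neither contains glucose or HbA1c, and capillary glucose is not among the monitored vital signs.

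**The concern.** A named toxicity of the study drug, an exclusion criterion and a possible ground for withdrawal all turn on glycaemic status. The protocol neither defines that status nor schedules a measurement of it. If glucose is checked only when a clinician has a reason to check, the chance of finding hyperglycaemia depends on whether diabetes is already known and on the practice of each hospital. Decompensation of diabetes also presupposes diabetes, so new hyperglycaemia in a patient without it has no named category.

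What is at stake is the safety comparison. With ascertainment left open, a small or absent difference between arms could reflect little harm or little testing, and the data would not separate the two. An analysis plan cannot repair this, because it cannot analyse values that were never collected.

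**Working it through.** No arithmetic underlies this point. The check is a reading of every list of assessments and variables for glucose, glycaemia or HbA1c.

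**Step 1. The four lists.**

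| List | Content | Glucose or HbA1c |
|---|---|---|
| Section 5.4.1, baseline procedures | blood count, coagulation with D-dimer, renal function, CRP, procalcitonin, ferritin, LDH, IL-6 | no |
| Section 5.4.2, 48-hourly procedures | the same | no |
| Independent variables, baseline blood tests | white cells, LDH, D-dimer, fibrinogen, IL-6, CRP, procalcitonin, ferritin, haemoglobin, platelets (10), plus SpO2/FiO2 (11 items) | no |
| Independent variables, follow-up blood tests | the same 10, or 11 items | no |

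The result is 0 of 4. The only place where the word glucose occurs in the protocol is a class of home medication, "Sodium-glucose cotransporter-2 inhibitors".

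**Step 2. Could glucose be hidden in another item?** A local renal panel might include it. However, renal function itself is in neither list of recorded blood tests, so a value obtained that way would still have no listed variable.

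**Step 3. The listed safety events against planned measurements.**

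| Listed event | Scheduled measurement that bears on it |
|---|---|
| Infection | procalcitonin, white cell count |
| Worsening hypertension | blood pressure |
| Gastrointestinal haemorrhage | haemoglobin |
| Delayed viral clearance | follow-up RT-PCR |
| Psychosis or mania | none; clinical recognition |
| Dyspepsia | none; clinical recognition |
| Diabetic decompensation | none; clinical recognition |

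Three named events rely on clinical recognition alone. Of these, diabetic decompensation is the one that turns on a laboratory value.

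**Step 4. What the remaining routes can catch.** Section 5.4.2 requires a doctor's review in person at least daily, follow-up under standard COVID-19 procedures, and extra assessment on significant change. Section 7 counts an abnormal laboratory finding as an adverse event, and section 7.1 sends all adverse events to the electronic case report form. These routes suit overt decompensation. They do not ensure detection of a raised glucose without symptoms: an abnormal value can be recorded only if a test was done, and the protocol does not require one.

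**The case against.** The strongest case on the other side is that these are inpatients seen daily by a specialised team, with a dedicated variable for diabetic decompensation, a residual safety category and mandatory recording of all adverse events. Other listed harms and other exclusions (psychotic disorder, active cancer, pregnancy) also have no listed test. Diabetic decompensation is neither a primary nor a secondary endpoint in its own right. The local panels and the guideline cited for follow-up may include glucose, and Figure 2 is not shown.

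Much of this stands, and it rules out stronger readings that a reader might infer:

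- **That this toxicity would be found only by chance, or that its ascertainment is nil.** Daily review and adverse event recording would probably pick up overt decompensation. The documents show that no glucose test is mandated. They do not show that none would be done, or that clinicians would test only patients with known diabetes.
- **That the exclusion cannot be applied.** History, comorbidities, concomitant treatments and examination at baseline allow a clinical judgement. The narrower point is that the exclusion cannot be verified from the specified tests and has no definition.
- **That new hyperglycaemia cannot be recorded.** Once observed, it can go under the residual category or as an adverse event. It lacks a named category and a measurement that would bring it to light.

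The objection does not supply uniform ascertainment. Two hospitals following unspecified usual care, with no definition of the event, do not give a like-for-like comparison of glycaemic harm.

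**Conclusion.** The point holds in this limited form. The protocol mandates and records no glucose measurement (0 of 4 lists, against 10 blood analytes or counts in each variable list) and does not define a safety event that it names. Overt decompensation is probably covered. Asymptomatic or moderate hyperglycaemia is not systematically covered, and a report of no excess would be weak evidence that the pulses are free of this harm.

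The primary efficacy analysis is not affected. The number of missed cases cannot be estimated, because the documents give neither the prevalence of diabetes in the sample nor the rate of usual-care glucose testing. The conclusion assumes that Figure 2 adds no glucose test. If usual care at both hospitals already measures glucose routinely, the gap narrows to the missing definition and the missing recorded variable.

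**What to change.** 1. Add plasma glucose to the panels in sections 5.4.1 and 5.4.2, run on blood already drawn, and to both blood-test lists under Independent variables.
2. Replace the single safety item with two: decompensation of known diabetes, and new hyperglycaemia in patients without known diabetes. The sponsor should choose a measurement definition for each in advance and compare each by arm. The exclusion criterion should be reconciled with the first definition.
3. For patients already enrolled, retrieve usual-care glucose values from the electronic health records, which section 9 names as a source, and report missingness by arm. The appendix gives 46 recruited at submission. Against the target of 72 in section 6.1, at most 72 − 46 = 26 would remain for prospective measurement if the target is kept, so retrieval matters.
4. State in the definition of the primary endpoint that glucose does not count towards laboratory progression, for which no criteria are now given.

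The cost is one assay on existing samples, a few case report form fields and a record search, with no extra visit or blood draw. The downside is that glucose values may hint at allocation to blinded clinicians. Step 4 keeps them out of the laboratory component of the endpoint but does not remove every influence on clinical judgement. The change concerns outcome measurement only; management of glucose stays with the sites.

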**Inclusion criteria:**

- Age ≥18 years
- Diagnosis of SARS-CoV-2 pneumonia confirmed by RT-PCR of nasopharyngeal swabs or sputum in accordance with the recommendations of the Spanish Ministry of Health
- History of symptoms compatible with COVID-19 ≥ 7 days
- At least one of the following: level of CRP >60 mg/L, IL-6 > 40 pg/ml and/or ferritin >1000 μg/L
- Provision of written informed consent.

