5.1 SECONDARY ENDPOINTS

- Mortality within 28 days after randomisation
- Proportion of patients admitted to the ICU within 28 days after randomisation
- Proportion of patients given tocilizumab as a rescue therapy within 14 days after randomisation
- Length of hospital stay in days
- Proportion of patients experiencing serious adverse events
- Proportion of patients with bacterial, fungal or opportunistic infections
- Changes in the laboratory parameters indicative of inflammation (CRP, IL-6, ferritin, and D-dimer) within 14 days after randomisation
- Viral clearance as assessed by nasopharyngeal RT-PCR at day 7.

Data collected will be entered into an electronic case report form; only study researchers will have access to these data and all the requirements in terms of data protection will be met.

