**5.2 RANDOMISATION**

After obtaining patient informed consent, the treatment strategy will be decided by block randomisation stratified by age into two groups (<75 and ≥75 years old). Randomisation will be performed with the randomizeR package in R software, using two blocks sizes (sized 4 and 6), with random permutation. The sequence will be generated by a unit (the Clinical Trials Platform of Navarrabiomed) independent of the researchers who will carry out patient recruitment and implement the protocol. These researchers will be blinded to the arm to which patients are to be allocated until the start of the intervention. The Clinical Trials Platform will inform the hospital pharmacy concerning the group allocation of each patient included in the trial.

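### The viral clearance swab is timed from the first PCR and limited by discharge, not tied to randomisation, so it may not measure clearance 7 days after randomisation

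*Protocol*

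**What the plan says.** Three places in the protocol bear on the timing of viral clearance.

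- **Secondary endpoints** (under Outcome measures): "Viral clearance as assessed by nasopharyngeal RT-PCR at day 7". No time origin is given. Four of the other seven endpoints in the list (mortality, ICU admission, tocilizumab rescue, laboratory changes) name randomisation, for example "Mortality within 28 days after randomisation". Length of stay, serious adverse events and infections do not.
- **Independent variables, safety-related events**: "Delay in viral clearance assessed by nasopharyngeal RT-PCR (7 days after the first RT-PCR").
- **Section 5.4.2, Follow-up**, the only place that schedules a swab: "A follow-up RT-PCR will be performed before administrative discharge and this is to be performed at least 7 days after the first PCR".

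The first PCR is not defined. The inclusion criteria require "Diagnosis of SARS-CoV-2 pneumonia confirmed by RT-PCR of nasopharyngeal swabs or sputum" and set no limit on how old that result may be. Section 5.2 places randomisation after consent: "After obtaining patient informed consent, the treatment strategy will be decided by block randomisation". The baseline assessment in section 5.4.1 includes no RT-PCR. Section 4.3 follows patients discharged early by phone. "Length of hospital stay in days" is itself a secondary endpoint.

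**The concern.** A clearance result at a fixed day is interpretable as a treatment comparison when both arms are swabbed at the same time after randomisation. Here the earliest permitted day depends on when the patient was first tested, and the latest on when the patient goes home. Nothing schedules a swab 7 days after randomisation.

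The two dependencies differ in kind. The interval from first PCR to randomisation is fixed before allocation. Time to discharge comes after allocation and may respond to treatment. If negativity becomes more likely with time, an arm that goes home sooner and is swabbed at discharge would look less often cleared with no drug effect on the virus. An arm that stays longer could have a real delay hidden.

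Delayed clearance is among the harms that the Background cites behind the advice against glucocorticoids, and it is listed as a glucocorticoid safety event. The trial should be able to report on it cleanly.

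**Working it through.** The protocol gives no figure to reproduce on this point, so the check is date arithmetic on its rules.

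**Inputs.** From section 5.4.2: the swab is at least 7 days after the first PCR and before administrative discharge, read here as hospital discharge. From the inclusion criteria and section 5.2: the diagnostic PCR precedes randomisation. Let k be the days from first PCR to randomisation and L the days from randomisation to discharge. The protocol gives neither, so the values below are assumptions.

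**Formula.** Earliest permitted day after randomisation = max(0, 7 − k). Latest = L. If L < 7 − k, no in-hospital swab meets both conditions.

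**Permitted swab days after randomisation**

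| k | L = 5 | L = 7 | L = 10 | L = 14 | L = 21 |
|---|---|---|---|---|---|
| 0 | none | 7 | 7–10 | 7–14 | 7–21 |
| 2 | 5 | 5–7 | 5–10 | 5–14 | 5–21 |
| 4 | 3–5 | 3–7 | 3–10 | 3–14 | 3–21 |
| 7 | 0–5 | 0–7 | 0–10 | 0–14 | 0–21 |

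**What follows.**

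1. Day 7 after randomisation is the only permitted day in one cell, k = 0 with L = 7. In every other cell with L of at least 7 it is one option among several.
2. With k = 5 or 6 the earliest permitted swab is 2 or 1 days after randomisation, within the three infusion days whether the first infusion is on the day of randomisation or the day after.
3. With k = 0 and discharge on day 5 there is no compliant swab, and phone follow-up does not supply one.
4. Take k = 2 in both arms, with discharge on day 7 in one and day 10 in the other. If all are swabbed at the earliest permitted day, both arms are swabbed on day 5: difference 0. If all are swabbed at discharge, the difference is 10 − 7 = 3 days. Under these two practices the gap in swab day runs from zero to the full difference in stay, and section 5.4.2 permits either.

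**Can it be repaired at analysis?** The listed variables include many dates (symptom onset, admission, discharge, ICU, each treatment) but none for the first PCR or the follow-up swab. Adjustment for swab day is therefore not assured.

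**The case against.** A fair defence has several parts.

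- **A three-way contradiction is more than the text shows.** A reader might infer it from the three places. The safety variable and section 5.4.2 share an origin (first PCR) and an interval (7 days); one states it as a minimum. The secondary endpoint gives no origin, and since only four of the other seven endpoints name randomisation, the first PCR could be its origin too. This stands. What remains is an unstated origin, an open upper limit, and no swab tied to randomisation.
- **Variation in k is mainly noise.** It is fixed before randomisation and balanced in expectation. This stands. Nor does "History of symptoms compatible with COVID-19 ≥ 7 days" show when patients were first tested; it only leaves room for an earlier test.
- **Swab day need not follow discharge.** A swab exactly 7 days after the first PCR complies, and administrative discharge is undefined. This stands: bias needs both a treatment effect on stay and swabs taken near discharge. Blinding does not remove that route, because stay can differ between blinded arms.
- **A numerical bias is tempting but unsupported.** Arms 1 to 3 days apart in swab timing, with negativity rising 3 to 8 points a day, would give 1 × 3 = 3 to 3 × 8 = 24 points. Every input is assumed. At the planned 30 per arm, the 95% half-width for a difference near 50% is 1.96 × √(2 × 0.25/30), about 25 points, so such a bias would be hard to distinguish from chance.
- **Delayed clearance is not singled out as the main safety concern.** The Background lists it with psychosis, diabetic complications, avascular necrosis and mortality, unranked, and then cites work suggesting no delay.
- **Analysis windows belong in the SAP.** That is true of windows and models, but the date a specimen is taken is fixed by the protocol. An SAP cannot recover a swab that was never scheduled.

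**Conclusion.** The point holds as a timing defect in a secondary and safety outcome. Followed as written, the protocol permits a swab from max(0, 7 − k) days after randomisation to discharge, so the result may not describe clearance 7 days after randomisation. The spread in k blurs the endpoint. The limit at discharge can bias the arm comparison, in either direction, under the two conditions already named. The documents give neither the PCR-to-randomisation interval nor the stay, so the size cannot be computed.

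The conclusion assumes that the first PCR is the diagnostic test and that administrative discharge means leaving hospital, which is natural because section 5.4.2 describes follow-up during admission. If administrative discharge means something else, the unstated origin and the lack of a swab tied to randomisation remain. A reader might infer that the trial will show false harm, or that delayed clearance will be missed; the documents establish neither. The point should be corrected, but it does not touch the primary endpoint.

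**What to change.** Reconcile the secondary endpoint, the safety variable and section 5.4.2 to one origin, randomisation, and one window: for example study day 7 ± 1, or the last in-hospital day if discharge is earlier. Use the single follow-up swab already planned. Add the dates of the first PCR and of the follow-up swab to the case report form.

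For the analysis, compare all randomised patients with a swab, accounting for actual swab day, and report the number without a swab by arm. Show swabs within day 7 ± 1 only as a sensitivity analysis: that subset excludes patients discharged earlier, so it is selected by a post-randomisation outcome and should not carry the main comparison.

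The cost is wording in three places and two date fields, with no extra swabs. Two limits remain. Patients discharged early still have earlier swabs, so some dependence on stay persists, and accounting for swab day reduces it only under assumptions about why patients left. Patients already recruited followed the old schedule. The Appendix reports 46 recruited when the protocol was submitted for publication, against 72 planned, so at most 72 − 46 = 26 could follow the new one. For the others, retrieving the two dates from hospital records would still allow swab day to be taken into account.
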